## **6. Study design**

The proposed study comprises a 2-arm (allocation ratio 1:1) pragmatic RCT to assess the efficacy of the EMA-based smoking cessation intervention and the EMA-based observational study. Throughout the 7-day participation, all recruited participants will complete an EoD survey and 4 time-based system-triggered EMA each day. The surveys will be prompted by a smartphone application (app) installed in their own mobile phones. The prompting time will be personalized and pre-scheduled by the participants. The information collected in the app will be used to develop an EMA-based intervention including a quit plan and 10-week quitting reminders and for an EMA-based observational study. I will randomly allocate half of the participants (intervention group) to receive the EMA-based intervention. All participants will then be contacted for a follow-up at 3-month and 6-month.

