## **8. Recruitment procedures**

In the outdoor recruitment sessions, the recruitment staff will approach and distribute souvenirs (e.g., a tissue pack) or leaflets to the smokers at outdoor smoking hotspots for 3-4 hours in daytime. If a smoker is willing to accept them and talk to the recruitment staff, the staff will advise the smoker to quit using the AWARD protocol and ask further questions related to eligibility. The AWARD protocol includes (1) **A**sk the smoking history, (2) **W**arn about the high risk (i.e., half of the smokers will die of smoking-related diseases), (3) **A**dvice to quit, (4) Introduce smoking cessation services and medications (**R**efer), and (5) Repeat the above advice (**D**o-it-again) (23). Our previous studies have shown that the AWARD protocol is a feasible and appropriate tool used by non-healthcare professionals to promote smoking cessation.

The promotion sessions will be organized at outdoor smoking hotspots, which will be selected from the public places in our funded project of Health Care Promotion Scheme (Project number 01170418). These locations cover New Territories, Kowloon, and Hong Kong Island, and the feasibility study supports that the number of subjects recruited in these locations will be higher than that in other places. Thus, they will be used in this study. Pre-promotion site visits and replacement of hotspots with reduced number of smokers will be done to ensure that the maximum number of smokers can be approached.

Eligible participants will be given more details of the study, and asked to consent to participation via an online form on Qualtrics. Then, the staff will assist the participants to install the EMA app on their mobile phones. Participants will need to complete a simple baseline questionnaire, which documents sociodemographic characteristics, smoking cues, smoking behaviours and contact information. Afterwards, the staff will ask the participants to select 7 consecutive days as the study period. Participants will be asked to set up the time they would like to receive the first time-based EMA from 6:00 am to 12:00 nn to undertake the regularly prompting EMA. For example, if a participant set the first prompt time at 9:00 am, he will be asked to complete an EMA survey at 9:00 am, 12:00 nn, 3:00 pm, 6:00 pm and an EoD survey at 9:00 pm. Then the staff will set up the EMA schedule in the app for the participants.

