## **11. Intervention**

***Smartphone application*** A EMA app will be developed to facilitate documentation of all smoking cues and smoking-related behaviors. After each recruitment, the staff will set up all EMA schedules of the participants in the back-end. Participants can then receive the EMA prompts and complete the EMAs. Participants will use the last 5 digits of their mobile phone numbers as identifier. They will use the app to complete an EoD survey and 4 time-based EMA each day in the 7 consecutive study days.

In each time-based EMA time window, the app will firstly prompt the user to answer questions on the smoking cues, smoking behaviours, and the association between smoking cues and smoking-related behavior, which only takes about 1 minute. If the user does not respond to an EMA prompt, 2 subsequent prompts will be generated. If these additional prompts are not responded to, the EMA will regard nonresponse as missing data. All data will be uploaded to our server immediately after each EMA completion.

The EMA questions on smoking cues cover 3 domains: mood, sleep, environmental triggers. The mood domain includes (1) irritable, depressed, restless, tension, stress, and other emotional cues related to smoking; Sleep domain includes insomnia symptoms for the last night. Environmental triggers include (1) social gathering; (2) family/friends/partner smoking; receive tobacco products/encouragement from others; (3) any other environmental smoking cues. Smoking-related behaviors include (1) nicotine craving (2) whether he/she has bought/consumed tobacco (traditional cigarettes, heated tobacco products and electronic cigarettes) in the past 3 hours (yes/no), (3) whether the tobacco consumption has been due to the exposure to the pro-smoking cues, and (4) other reasons of tobacco consumption (e.g., kill time, habit, leaving a place where smoking is not allowed). EoD survey includes (1) daily tobacco consumption; (2) time to consume the first cigarette after waking; (3) all EMA questions; (4) tobacco control policy questions which include daily exposure to health warnings on their tobacco pack/POS tobacco display/exposure to hotspot.

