#### **14. Statistical analysis**

Intention-to-treat approach will be used to include all consented participants in the analysis and assume non-respondents at the 3-month follow-up as smokers. Chi-squared and t-tests will be used to compare sociodemographic and smoking characteristics of participants to assess the balance between intervention and control group.

The primary comparison is the prevalence of tobacco abstinence and the score of IBC-S between the EMA-based smoking intervention group and the control group. Logistic regression model and linear regression will be used to compare the 7-day PPA and the score of IBC-S between intervention and control group at 3 months, respectively. We will also use multiple logistic regression and multiple linear regression adjusted for imbalance socio-demographic smoking characteristics assessed at baseline to account for imbalances in baseline characteristics.

We will transfer checklist options of smoking cues to binary outcomes. For example, an EMA question asked 'In the past 3 hours, have you been exposed to (check all that apply)' followed by these checklist options: family smoking; friends smoking; partner smoking; receive tobacco products from others; receive encourage of smoking from others). We will recode response into a series of dichotomous variables. Generalized estimating equation analysis will be used to examine the causal relationship between smoking cues and smoking-related behaviors in all participants. A linear mixed model will be used for the association analysis when the outcome is not binary.

Direct operating costs will include app development, salary (of nurses and research assistants), recruitment, telephone follow-up, and publicity items. Costs for study design, analysis, report

writing, and irrelevant administration will be excluded. The cost per successfully recruiting a smoker to participate will be calculated by dividing the total cost by the number of smokers who have joined. Similarly, cost per participant who use smoking cessation aids and per quitter at 3-month follow-up will be calculated.

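### The fixed 3-hour look-back lets the first EMA window of the day include sleep, and with no wake time recorded this can distort same-window cue-behaviour odds ratios in either direction

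*Protocol*

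**What the plan says.** Protocol section 14 recodes checklist answers into yes/no variables. Its example cue item begins "In the past 3 hours, have you been exposed to (check all that apply" and lists smoking by family, friends or partner, and receiving tobacco or encouragement from others. Section 11 asks whether the participant "has bought/consumed tobacco (traditional cigarettes, heated tobacco products and electronic cigarettes) in the past 3 hours (yes/no". The two items share one look-back, and no separate wording is given for the first prompt of the day.

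On timing, section 6 says: "The prompting time will be personalized and pre-scheduled by the participants". Section 8 gives the permitted range: "Participants will be asked to set up the time they would like to receive the first time-based EMA from 6:00 am to 12:00 nn". Its worked example has the participant "complete an EMA survey at 9:00 am, 12:00 nn, 3:00 pm, 6:00 pm and an EoD survey at 9:00 pm", so prompts are 3 hours apart. There are 4 time-based EMAs and one end-of-day survey a day for 7 days.

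The sleep domain in section 11 covers insomnia symptoms of the previous night. The end-of-day survey asks how long after waking the first cigarette was consumed. That is an interval, not a clock time. Wake time is not listed.

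Section 14 then applies GEE to the cue-behaviour relationship, which it calls causal. It does not say whether the cue is taken from the same window as the behaviour or from the one before.

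**The concern.** A 3-hour window ending at 6:00 am runs from 3:00 to 6:00. In the protocol's own 9:00 am example it runs from 6:00 to 9:00. Participants with different wake times can thus give the same recorded answer from very different time at risk. Someone who woke at 5:45 and answers at 6:00 has had 0.25 hours in which to meet a cue or smoke. Someone who woke at 7:30 and answers at 9:00 has had 1.5 hours. Someone who woke at 6:00 and answers at 9:00 has had the full 3 hours. All three are coded on the same 0/1 scale and cannot be told apart afterwards from the listed items.

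Time awake acts on both variables. Windows spent asleep add records with neither cue nor smoking, which pushes a same-window odds ratio above 1. A cigarette soon after waking, before any social cue, adds smoking without a cue and pushes it below 1. Aim 2 is to estimate these associations in the local context, and section 4 wants such data to inform tobacco policy. An association produced partly by the measurement window would weaken that use.

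**Working it through.** The protocol states no odds ratio, power or error rate for the current cue analysis, so there is no figure to reproduce. The check asks what a pooled same-window analysis returns when the true odds ratio is 1.00.

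**Inputs from the protocol.** Look-back 3 hours for cue and behaviour (sections 11 and 14); first prompt from 6:00 am to noon, later ones every 3 hours (section 8); 4 time-based EMAs a day, so the first is 1/4 of time-based records, or 1/5 if the end-of-day survey is pooled; 440 participants (section 7).

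**Assumptions, not in the protocol.** Probability of a cue (p) and of smoking (q) in a fully awake window; time from waking to first prompt; cue and smoking independent given time awake.

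**Formula.** For window types with weight w, cells are a = Σwpq, b = Σwp(1−q), c = Σw(1−p)q, d = Σw(1−p)(1−q), and OR = ad/(bc).

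**1. Some first windows wholly asleep.** Take p = 0.4, q = 0.7 and a share f = 25% of first windows asleep. The asleep weight is 0.25/4 = 0.0625 and the awake weight 0.9375.
- a = 0.9375×0.4×0.7 = 0.2625
- b = 0.9375×0.4×0.3 = 0.1125
- c = 0.9375×0.6×0.7 = 0.3938
- d = 0.9375×0.6×0.3 + 0.0625 = 0.2313
- OR = 0.2625×0.2313/(0.1125×0.3938) = 1.37

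For f = 10%, 50% and 100% the result is 1.14, 1.79 and 2.85. At f = 25%, with p from 0.2 to 0.6 and q from 0.5 to 0.85, it runs from 1.17 to 2.11.

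**2. Partly awake first windows, constant hourly rates.** With t hours awake (at most 3), the first-window probabilities are 1−(1−p)^(t/3) and 1−(1−q)^(t/3), averaged over t and pooled with three fully awake windows.

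| Waking to first prompt (uniform) | p 0.2, q 0.7 | p 0.2, q 0.85 | p 0.4, q 0.85 |
|---|---|---|---|
| 0–1 h | 1.69 | 2.16 | 2.44 |
| 0–3 h | 1.27 | 1.45 | 1.56 |
| 1–4 h | 1.06 | 1.10 | 1.12 |
| 3 h or more | 1.00 | 1.00 | 1.00 |

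**3. First cigarette after waking.** Take every first window half awake, p = 0.4 and q = 0.7 elsewhere, and first-window smoking of 0.9. The first-window cue probability is 1−0.6^0.5 = 0.2254.
- a = 0.75×0.28 + 0.25×0.2254×0.9 = 0.2607
- b = 0.75×0.12 + 0.25×0.2254×0.1 = 0.0956
- c = 0.75×0.42 + 0.25×0.7746×0.9 = 0.4893
- d = 0.75×0.18 + 0.25×0.7746×0.1 = 0.1544
- OR = 0.2607×0.1544/(0.0956×0.4893) = 0.86

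If first-window smoking is instead 0.7, the same as elsewhere, OR = 1.00.

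Adding to the 0–3 h row a share who smoke within 30 minutes of waking (probability rising linearly over those 30 minutes) lowers the three values to 1.10, 1.25 and 1.32 at 50%; 1.03, 1.17 and 1.21 at 70%; and 0.96, 1.07 and 1.10 at 90%. With the first prompt 0.5–3 h after waking and a 70% share, all three lie between 0.95 and 1.00.

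**4. What removes it.** GEE was fitted to simulated data (440 × 7 days × 4 EMAs, exchangeable correlation, true OR 1.00, p = 0.4, q = 0.7, 20 runs), with 25% of participants asleep throughout the first window and 50% awake for 40% of it.
- Unadjusted, same window: 1.50
- Adjusted for prompt number: 1.19
- First EMA dropped: 1.00
- Cue lagged by one prompt: 1.00 (1.00 to 1.02 across all scenarios tried)

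For the 0–3 h row, logistic regression on 400,000 simulated windows gave 1.27, 1.47 and 1.57 crude; 1.09, 1.19 and 1.24 with a first-prompt indicator; and 1.00, 1.02 and 1.01 with log hours awake added.

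**The case against.** The strongest reply is that the distortion needs a particular analysis which the protocol does not fix. Section 4 values measurements at different time points for temporal ordering, and the tobacco pilot analysed subsequent behaviour from EMA pairs. A cue lagged by one prompt would remove the problem. Lag and covariates may be settled in an analysis plan that is not shown. This stands, and their absence is no fault of the protocol. But section 4 now prefers separate to paired assessments, so a same-window analysis is a natural reading. The item wording and prompt range are fixed in the protocol, and no later plan can model hours awake that were never asked about.

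Participants also choose the prompt, and many may choose a time well after waking. This too stands: the window can include sleep, but how often is unknown.

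Three stronger readings are tempting and not supported:

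- **The odds ratios will be inflated.** Both answers are certain to be no only in a window spent wholly asleep. For daily smokers, the first cigarette after waking can reverse the direction.
- **A true null would almost always be rejected at the planned size.** That follows only if one assumed spread of wake times, a constant smoking rate and an unadjusted same-window model all hold.
- **The artefact is as large as the pilot odds ratio of 1.47 and so could hide it.** The pilot figure relates point-of-sale displays to subsequent consumption. In the current plan that exposure is a daily end-of-day item, outside the 3-hour example checklist. Cue, window and analysis all differ.

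**Conclusion.** The point holds as a measurement weakness in the observational aim. Up to one time-based record in four can contain time asleep, and the listed items do not let an analyst recover time at risk. In a pooled same-window GEE this can distort the cue-behaviour odds ratios, often upward but possibly downward. Under a true value of 1.00, the main scenarios give about 0.9 to 2.4. That range is illustrative and not a bound: it rests on assumed wake times, cue and smoking rates, and early-morning smoking, and more extreme inputs go beyond it, as the 2.85 with every first window asleep shows. It shrinks to 1.00 when first windows are fully awake or the cue is lagged by one prompt. The randomised comparison of abstinence and IBC-S is not touched. This is a cheap improvement worth making, not a threat to the trial's main conclusion.

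**What to change.** In the first EMA of each day, ask what time the participant woke, and word the look-back for cue and behaviour as *since you woke up, or in the past 3 hours if that is shorter*. Where cue and behaviour are analysed within the same window, adjust for prompt number and hours awake in that window. Report a sensitivity analysis without the first daily EMA, or with the cue lagged by one prompt.

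If the app can no longer be changed, report the analysis without the first EMA. Adjusting for prompt number alone is not enough when time awake differs between people, since 1.19 remained of 1.50 in the simulation above.

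The cost is one short question and a wording change, a few seconds of extra burden a day, and some loss of precision from partly awake windows. Dropping the first EMA gives up a quarter of the time-based records and the early part of the day, which is why recording wake time is the better course while the app can still be altered.

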Participants will be encouraged to improve compliance via WhatsApp reminders if their compliance rate drops to 50% or below in the first 3 study days. To increase uptake and compensate the time spent by the participants, a small amount of cash incentive is needed. All participants will be given a HK\$50 gift voucher for the completion of baseline survey. They will be rewarded a HK\$ 15 gift voucher for completing 3 time-based EMA surveys within each day. They will be further rewarded a HK\$ 10 gift voucher for completing all surveys in each day. In addition, participants will be further rewarded HK\$ 25 gift voucher for completing more than 80% of 7 days time-based EMA surveys. Participants who complete biochemical validation at 3 months or 6 months follow up will obtain an additional HK\$50 gift voucher.

**EMA-based intervention** Based on the EMA of each participant, a trained research nurse will review their (1) nicotine dependence; (2) intensity and frequency of reported cravings; and (3) the impact of exposure to pro-smoking cues on smoking behaviors. A personalized quit plan will be developed based on tailored suggestions from the US clinical practice guideline for smoking cessation, Smoking Cessation, Smoking Cessation Information Kit (published by Department of Health), the theory of Health Action Process Approach, and the self-determination theory. Our recent studies showed that interventions based on these theories are effective (22, 24). Half of the randomly selected participants (intervention group) will receive this quit plan via a nurse-led phone call, email, and WhatsApp. The nurse will then design a quit plan including (1) self-help techniques on handling craving; (2) suggestions to avoid the reported pro-smoking cues; (3) whether to quit progressively or abruptly; (4) referral for existing smoking cessation service; and (5) instruction of using over-the-counter (OTC) nicotine replacement therapy (NRT), if OTC-NRT is preferred by the participant. Participants will then receive tailored quitting reminders via instant messaging social media (i.e., WhatsApp, WeChat) and voluntarily discuss their quit plan with the nurse in the subsequent 10 weeks.

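### The cue checklist shown in section 14 has no 'none of these' choice, so a skipped list looks like no exposure and could bias the Aim 2 cue associations in either direction

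*Protocol*

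**What the plan says.** Protocol section 14 explains how the cue questions become analysis variables. It introduces an illustration with "For example, an EMA question asked", gives the stem "In the past 3 hours, have you been exposed to (check all that apply", and lists as options "family smoking; friends smoking; partner smoking; receive tobacco products from others; receive encourage of smoking from others". It continues: "We will recode response into a series of dichotomous variables". The recoded cues then enter a generalized estimating equation (GEE) analysis, described as examining a causal relationship between cues and smoking-related behaviour in all participants. That is Aim 2 in section 2.

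Section 11 (Smartphone application) describes the behaviour item differently: whether tobacco was bought or consumed "in the past 3 hours (yes/no", that is, with an explicit negative answer. The missing-data rule in the same section concerns prompts: "If these additional prompts are not responded to, the EMA will regard nonresponse as missing data". No rule is given for an item left blank inside a submitted survey.

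Section 11 also sets the payments: HK$15 as a "gift voucher for completing 3 time-based EMA surveys within each day", HK$10 as a "gift voucher for completing all surveys in each day", and HK$25 for passing 80% of the time-based surveys over the week. No check on answer quality is described.

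**The concern.** In a check-all list without a 'none' choice, a participant who met no listed cue can report that only by ticking nothing. A participant who hurries past the item leaves the same trace. Once each option is recoded to two levels, both records fall naturally into the unexposed level.

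Exposure is the independent variable for the whole of Aim 2. Cue and behaviour are reported in the same survey over the same 3-hour window, so one careless survey can supply both a false exposure value and an unreliable outcome value. If hurried respondents deny smoking, the unexposed, non-smoking cell is inflated and the odds ratio rises. If they affirm smoking, it falls. Payment for completion, with no stated quality check, gives some reason to expect such surveys. The nurse also reviews the reported cues when preparing the quit plan, so a skipped list could hide a cue there as well.

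**Working it through.** The protocol gives no figure on this point, so there is nothing to reproduce. The check is a mixture of genuine and skipped lists in a 2×2 table.

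**Inputs from the protocol**
- Five options and no 'none' choice in the item shown (section 14).
- A yes/no behaviour item over the same 3 hours (section 11).
- Payment for EMA completion of up to 7 × (15 + 10) + 25 = HK$200 per person (section 11).

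**Assumed inputs (not in the protocol)**
- Cue present in c = 0.30 of genuine windows, smoking in s = 0.80, no true association.
- A share b of submitted surveys has a skipped list coded 0; b = 0.02, 0.05 or 0.10.
- A share q of those surveys answers 'yes' to smoking.

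**Cells**
- Exposed, smoked: (1−b)cs = (1−b) × 0.24
- Exposed, not smoked: (1−b)c(1−s) = (1−b) × 0.06
- Unexposed, smoked: (1−b)(1−c)s + bq = (1−b) × 0.56 + bq
- Unexposed, not smoked: (1−b)(1−c)(1−s) + b(1−q) = (1−b) × 0.14 + b(1−q)

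The odds of smoking among the exposed are 0.24/0.06 = 4, so

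OR = 4 × [(1−b) × 0.14 + b(1−q)] / [(1−b) × 0.56 + bq]

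**Results**

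| Smoking answer in skipped surveys | b = 2% | b = 5% | b = 10% |
|---|---|---|---|
| All 'no' (q = 0) | 4 × 0.1572/0.5488 = 1.15 | 4 × 0.183/0.532 = 1.38 | 4 × 0.226/0.504 = 1.79 |
| Exactly half 'no' (q = 0.5) | 4 × 0.1472/0.5588 = 1.05 | 4 × 0.158/0.557 = 1.13 | 4 × 0.176/0.554 = 1.27 |
| Genuine rate (q = 0.80) | 1.00 | 1.00 | 4 × 0.146/0.584 = 1.00 |
| All 'yes' (q = 1) | 4 × 0.1372/0.5688 = 0.96 | 4 × 0.133/0.582 = 0.91 | 4 × 0.126/0.604 = 0.83 |

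The direction turns on whether q lies below or above s.

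**Range.** With no true association and q = 0, the formula reduces to OR = 1 + b/[(1−b)(1−c)(1−s)]. Over b = 5 to 20%, c = 20 to 60% and s = 50 to 80%, it runs from 1.13 to 4.12. With q = 1 over the same grid, the odds ratio runs from 0.44 to 0.92.

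**A true association.** Take an assumed true odds ratio of 1.47, cue 40%, smoking 70% and b = 10%. The genuine cells are 0.299, 0.101, 0.401 and 0.199. The observed odds ratio is 2.29 if q = 0, 1.44 if q = 0.70 and 1.15 if q = 1. So careless answers unrelated to smoking dilute the estimate only slightly; the damage comes from a smoking answer that is itself careless.

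**Limits.** The table pools surveys, ignores covariates and takes cue and behaviour from the same survey. It shows the mechanism and its scale; it does not forecast the trial's estimate.

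**The case against.** The item is one illustration of recoding, and the questionnaire is not shown. The EMA content in section 11 is wider, covering mood, sleep and other environmental triggers. A reader might infer that no cue checklist in the app has a 'none' option, or that the app lets users pass an item unanswered. The protocol says neither. A reader might also infer that the protocol orders blanks to be coded as unexposed. It does not; that is the natural result of the stated recoding. Item-level coding rules could sit in a SAP or data-management plan that is not at hand. All of this stands and limits the point to the item shown and to any others built the same way.

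Three further readings go too far:
- **A spurious positive association is to be expected.** This needs hurried respondents to deny smoking more often than genuine ones do; otherwise the bias is nil or reversed. No skip rate is given.
- **The pilot odds ratios of 1.47 and 1.57 (section 4) show that effects of this size could be artefact.** They concern point-of-sale displays and subsequent behaviour, and 1.57 is for craving. Here point-of-sale exposure is an end-of-day question, outside the list shown.
- **The data could not be repaired at all.** Excluding very fast surveys would help in part, if response times are recorded. The quit plan is also delivered through a nurse-led call, with voluntary discussion over 10 weeks, so it need not rest on tick-boxes alone.

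The answer that the SAP may handle it is incomplete. A coding rule cannot separate two kinds of blank that the instrument records identically. Treating every blank as missing would also discard every window in which a participant truly met none of the listed cues.

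**Conclusion.** The point holds for the item as shown. Its format does not distinguish no exposure from no answer, and the protocol states no rule for a blank item within a submitted survey. If lists can be skipped, the cue associations could be biased in either direction. Under the assumed 30% cue and 80% smoking prevalence with no true association, 10% skipped lists would move the odds ratio to anywhere from 0.83 to 1.79, depending on how smoking is answered in those surveys. At 2% the range is 0.96 to 1.15. The true skip rate, the prevalences and the behaviour of hurried respondents are all unknown.

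A reader might take this as a threat to the trial's main result. It is not: abstinence and IBC-S at 3 months are compared between randomised arms and do not use the cue variables. The point is a worthwhile correction to the Aim 2 instrument and its coding, made cheaply before data collection.

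**What to change.** For the item shown in section 14, and for any other cue checklist that lacks one, add a compulsory 'none of these' option or ask each cue as yes/no, so that the survey cannot be submitted without an answer. In section 14, state that a list with neither a cue nor 'none' ticked is coded as missing, not 0. If the app records response times, add a sensitivity GEE that excludes implausibly fast surveys, with the threshold set in advance. If every cue checklist already has such an option, it is enough to say so in section 14 and give the coding rule.

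The cost is one option per checklist in the app, a sentence or two of protocol text, and one extra tap per checklist for the participant (more if every cue becomes a yes/no). A participant can still tick 'none' carelessly, so the change separates blanks from negatives but does not guarantee accurate answers; the speed-based sensitivity analysis addresses part of that.
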